#### Planned subgroup analyses

An examination of whether any difference in outcomes between control and intervention arms varies by sex, weight status at baseline, ethnic mix of the school and socio-economic factors will be undertaken. Within the intervention arm, we will also look at differences in outcome by fidelity of implementation (broadly classified as low, medium or high).

The significance of subgroup effects will be assessed by tests of interactions of covariates and the treatment effect. The study will have low power to detect all but the largest differences in subgroups.

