#### Trial aims and objectives

The main aim is to assess the clinical and cost-effectiveness of the 12-month childhood obesity prevention intervention programme, developed and refined in the BEACHeS study, using usual practice in primary schools as the comparator. Intervention effects will be examined at 3 and 18 months post-intervention completion. Cost-effectiveness of the intervention will be assessed from a societal perspective. In addition, differences in intermediate and final outcomes will be explored by sex, ethnicity, socioeconomic status and weight status. We will also use a variety of methods to describe the implementation of, and adherence to, intervention components [17].

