## Methods

### Study setting and participant eligibility

All state primary schools in the West Midlands (UK) which included school years 1 to 5 (children aged 5 to 10 years) and that were within a 35 mile radius of the University of Birmingham were eligible for inclusion (n = 980). To ensure sufficient representation in the sample to enable sub-group analysis by minority ethnic group, school populations were stratified by ethnic mix including White, South Asian (comprising Indian, Bangladeshi and Pakistani) and Black (including African and Caribbean), with the remainder being classified as “Other” ethnicity. School populations were dichotomised as being in the top 80th percentile in terms of South Asian or Black pupil representation, or not. The sampling strategy used a weighted random sample so that schools with a higher minority ethnic population (in top 80th percentile for South Asian or Black) had an increased chance of being sampled with a ratio of 3:1. Given the relatively large number of clusters (>50) the sampling strategy was also balanced to take account of three other important factors to ensure a range of characteristics are represented. These were: proportion of children eligible for free school meals (FSM) as an indicator of socio-economic make-up of the pupils, school size and urban/rural location of the school. Using this method, 200 schools were selected and ordered using a random number generator. Of these, 7 were excluded as they did not fit the eligibility criteria. The remaining schools were sequentially invited to participate, and 148 were approached until the required sample size (54 schools) was achieved. Of the 148 schools approached, 4 did not respond and 90 declined to participate.

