### Data collection methods

Pupils’ date of birth, sex, ethnicity and postcode (to derive a proxy measure for deprivation) data are obtained from parent questionnaire, or if not available, from school records. Assessments are undertaken in school by trained research staff, using standardised procedures (available on request) and validated instruments at baseline and follow-up time points. In addition, parents of participating children are asked to complete questionnaires at each time point. These cover questions on child and parent demographics, dietary, sedentary, physical and sleep activity habits, home food environment, perceived neighbourhood environment and proximity to food and leisure facilities, family cooking habits and participation in leisure activities.

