### Planned statistical analysis

Trial analyses will be undertaken after the second follow-up measures are completed and there will be no interim analyses.

The baseline pupil (including sex, ethnicity, deprivation [based on IMD scores derived from home postcode] anthropometric measures, dietary intake, physical activity levels, psychological variables) and school level characteristics (school size, ethnic mix of pupils and % eligible for FSM) will be summarised by control and intervention arms, using numbers and proportions, means and standard deviations or medians and inter-quartile ranges.

Analyses of outcomes will be by intention to treat. As randomisation will be at the school (cluster) level, appropriate statistical methods to account for the clustering within schools (detailed below) will be used in the analysis. Analysis of outcomes will be for both 3- and 18-month follow-up stages.

We will use a mixed model ANCOVA with follow-up outcome values as the dependent variable and baseline values and treatment arm as the independent variables, to investigate effectiveness. These will be fitted using mixed models in STATA to allow for clustering. We will allow for clustering at the school level and explore the possibility of allowing for an additional level of clustering at the class level.

The primary analysis will be adjusted for baseline values for all outcomes. Secondary analysis will additionally adjust for pre-specified baseline school and child level covariates. These will include school level factors which were used in the randomisation (school size, % pupils eligible for free school meals, ethnic mix of pupils) and pupil level factors (sex, baseline BMI z-score, ethnicity, deprivation from home postcode, baseline total energy intake and baseline total physical activity). We will not adjust for age as all children will be of a very similar age. We will adjust at the school and pupil level for both ethnicity and deprivation as the school population is expected to differ from the consented study population.

Outcomes are either binary (e.g. non-overweight vs. overweight), or continuous (e.g. BMI z-score or energy expenditure), and therefore either log or linear link functions will be used, with transformations where appropriate to accommodate any non-normality. All model assumptions will be checked. We will report both relative and absolute treatment effects.

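### The ethnic subgroup test uses the school's ethnic mix only, whereas the objective is to explore effects by ethnicity and each child's ethnicity is recorded

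*Protocol article*

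**What the plan says.** Four parts of the protocol article bear on this.

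- **Trial aims and objectives:** "differences in intermediate and final outcomes will be explored by sex, ethnicity, socioeconomic status and weight status". Ethnicity stands beside sex and weight status, which are attributes of the child.
- **Study setting and participant eligibility:** the purpose of the weighted sampling was "to enable sub-group analysis by minority ethnic group". The stratified and sampled unit was the school: those with a high South Asian or Black share "had an increased chance of being sampled with a ratio of 3:1".
- **Data collection methods and Planned statistical analysis:** pupils' "sex, ethnicity and postcode (to derive a proxy measure for deprivation) data are obtained from parent questionnaire", with school records as the fallback. Pupil ethnicity is then listed for the secondary model among the "pupil level factors (sex, baseline BMI z-score, ethnicity, deprivation from home postcode". Ethnicity and deprivation are adjusted for at both levels because "the school population is expected to differ from the consented study population".
- **Planned subgroup analyses:** the article will examine whether the treatment effect "varies by sex, weight status at baseline, ethnic mix of the school and socio-economic factors will be undertaken", using tests of interaction. It adds that power will be low for all but the largest subgroup differences.

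No interaction between arm and the child's own ethnicity is named anywhere in the article.

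**The concern.** The objective and the named effect modifier are different variables. An arm × school-mix interaction asks whether the programme works differently in schools with more minority pupils. The objective, read with its neighbours in the list, asks whether it works differently for children of different ethnic groups. The two coincide only if school composition does not itself modify the effect. That cannot be taken for granted here, because the Trial intervention section lets schools adapt delivery to local circumstances.

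The equity question is at stake. The Background faults earlier trials for rarely considering it, and the sampling was weighted to support it. If schools are ethnically mixed, a real difference between children of different groups appears only in part in a contrast between schools, so a null result on school mix would say little about children. The subgroup section positively names the modifier, so this is more than a detail left to an analysis plan: a plan that follows the article inherits the mismatch, and one that uses child ethnicity departs from it.

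**Working it through.** **Inputs from Justification of sample size:** 1000 children in 50 schools at follow-up (20 per school, 25 schools and 500 children per arm); before-after correlation 0.9; ICC 0 to 0.04; cluster size mean 25, SD 23, so CV = 23/25 = 0.92. **Assumed, because not stated:** BMI z-score SD 1, two-sided 5%. Residual variance = 1 − 0.9² = 0.19.

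**The plan's own figure.** Design effect at ICC 0.04 = 1 + ((0.92² + 1) × 20 − 1) × 0.04 = 2.437. SE of the main effect = √(2 × 0.19 × 2.437/500) = 0.043. For a difference of 0.25, 0.25/0.043 = 5.8, so power exceeds 99%, consistent with the stated figure of over 90%. For 0.125, power is about 83%, consistent with the stated figure of over 80%. The article gives no figure for the ethnicity subgroup.

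**Interaction, illustrated.** Further assumptions: 50 equal schools of 20; half the schools in each arm high-mix; a binary minority indicator; minority share 80% in high-mix and 20% in low-mix schools; random-intercept model. At ICC 0.04 the between-school variance is 0.0076 and the within-school variance 0.1824.

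*By school mix.* Four cells of 250 children: SE = √(4 × 0.19 × (1 + 19 × 0.04)/250) = √0.00535 = 0.073. Detectable at 80% power = 2.80 × 0.073 = 0.205, as a difference between school types. If the effect follows the child's own ethnicity, the school contrast shows only 0.8 − 0.2 = 0.6 of it, so the detectable child-level interaction is 0.205/0.6 = 0.34.

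*By child ethnicity.* Per arm, the within-school sum of squares is 500 × 0.16 = 80 and the between-school sum is 500 × 0.09 = 45. Information = 80/0.1824 + 45/(0.1824 + 20 × 0.0076) = 438.6 + 134.6 = 573.2. SE = √(2/573.2) = 0.059; detectable 0.165.

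*At ICC 0.* Both SEs equal √(4 × 0.19/250) = 0.055. Detectable: 0.154 by child ethnicity and 0.154/0.6 = 0.257 by school mix. The precision gap has gone; the dilution has not.

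**Sensitivity to the assumed shares, ICC 0.04:**

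| Minority share, high/low-mix schools | Detectable child-level interaction, by child ethnicity | By school mix |
|---|---|---|
| 60/40 | 0.153 | 1.03 |
| 80/20 | 0.165 | 0.34 |
| 90/10 | 0.180 | 0.26 |
| 100/0 | 0.205 | 0.205 |

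For a true child-level interaction of 0.125 at 80/20, power is about 56% by child ethnicity and 17% by school mix.

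**A limit on the child-level figure.** The SE of 0.059 borrows between-school information, so it too assumes no contextual effect. With the arm × school-mix interaction in the same model, only within-school information remains: SE = √(2/438.6) = 0.068, detectable 0.19.

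**Small groups.** With an assumed 50% White and within-school comparison, the Black-versus-White interaction has SE = √(2 × 0.1824 × (1/250 + 1/n)), where n is the number of Black children per arm. This gives 0.071 if 20% are Black (n = 100), 0.080 if 15% (n = 75) and 0.094 if 10% (n = 50). At the lower shares it is larger than the 0.073 for school mix.

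**The case against.** The strongest reply is that school mix is a sensible modifier here. Schools were stratified, sampled and randomised, delivery can be tailored by school, and the subgroup matches the sampling stratum. The objective says only that differences will be explored and does not specify the pupil level. The article already warns of low subgroup power, and no primary conclusion rests on this test. All of that stands. It supports keeping the school-mix analysis, but does not make it the analysis of children's ethnicity.

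A reader might infer more than the documents support:

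- **That the oversampling selected children by ethnicity.** It did not: "To ensure sufficient representation in the sample to enable sub-group analysis by minority ethnic group, school populations were stratified by ethnic mix". Only the stated purpose concerns minority ethnic groups.
- **That the planned test cannot answer the equity question at all.** It can, if school composition has no effect of its own; the difficulty is that this must be assumed.
- **That the protocol concedes school mix to be a poor proxy for the child.** It says only that the school and consented populations are expected to differ, without a size, as the reason for adjusting at both levels.
- **That the SE is 1.6 times larger with school mix.** That ratio sets 2 × √(2 × 0.19 × 2.437/500) = 0.086 against √(4 × 0.19 × 0.96/250) = 0.054. The second needs every school to be half minority; the first needs half the schools to be high-mix. Both cannot hold, and the first uses the sample-size design effect rather than the planned mixed model. At 80/20 and ICC 0.04 with equal clusters the ratio is 0.073/0.059 = 1.24, and at ICC 0 it is 1.

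**Conclusion.** The mismatch holds as a matter of text. The objective is by ethnicity, child ethnicity is collected and modelled, and the only ethnic modifier named for the interaction tests is the school's mix. That test informs the objective only under the assumption of no contextual effect, and it dilutes a child-level interaction wherever schools are mixed.

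The size is conditional. The contrast of 0.34 with 0.165 rests on SD 1, ICC 0.04, equal clusters, a binary modifier and an 80/20 mix, and of these only the ICC comes from the protocol. Dilution is the firmer part, since it persists across the whole ICC range and vanishes only if schools are fully segregated. The precision gain is modest, absent at ICC 0, and may not reach contrasts for small groups. Unequal cluster sizes were left out of the interaction calculation; they would mainly penalise the school-level test further. The point concerns a secondary, low-power analysis and leaves the primary comparison untouched.

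**What to change.** In Planned subgroup analyses, name the interaction of arm with the child's own ethnicity (White, South Asian, Black, Other) in the mixed model as the ethnicity subgroup test. Keep school ethnic mix as a separately labelled contextual analysis. State whether the two interactions are fitted together, since that decides whether the child-level estimate is free of school-composition effects, and which of them counts among the primary subgroup comparisons tested at 5%.

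The change is one of wording. Child ethnicity is already collected, and Trial status places the analysis after June 2015, later than the article's publication in May 2015. The cost is one additional interaction test of low power, with imprecise contrasts for the smaller groups, to be reported as such.

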### Economic evaluation

The economic evaluation will estimate the incremental cost and incremental benefit of the WAVES study intervention compared to usual current practice, from a NHS/educational service perspective. Additional wider perspectives, such as inclusion of family members, will be explored as part of a sensitivity analysis. A within-trial analysis will estimate the cost-effectiveness at 18 months assuming that the intervention is in a ‘steady state’ and thus will not include set up or implementation costs. A longer term analysis will estimate the cost effectiveness using a decision-analytic model.

The within-trial analysis will adopt a micro-costing approach to estimate the costs of each intervention component. Trial report forms and school logbooks will collect resource use information for staff time, materials, transport, and equipment, combined with unit cost data to estimate the incremental intervention mean cost per class, and per child. Sensitivity analysis will explore intervention fidelity, and the inclusion/exclusion of categories of cost e.g. family members, set up, implementation. Quality of life will be measured using the Child-Health Utility 9D instrument and expressed as QALYs. Cost-effectiveness will be measured using both the effectiveness outcomes (BMI z-score, proportion overweight/obese) and QALY outcomes.

The long-term cost effectiveness analysis will use a decision-analytic model to predict the cost-savings and outcomes from preventing overweight/obesity in childhood. Model parameters will be informed by a literature review and will map outcomes from childhood to adulthood. Extensive sensitivity analysis will be carried out, to test for the robustness of the conclusions to assumptions made in the modelling, and to sampling variation in the data used in the construction of the model. Costs and benefits will be discounted at the standard rate (3.5%).

### Trial status

The trial started recruitment of schools in January 2011, and of pupils from March 2011. Intervention delivery was completed in July 2013. Final follow-up measurements will be completed in April 2015. Data analysis will commence following data cleaning (after June 2015). The expected report date is November 2015.

## Discussion

To our knowledge, the WAVES study is the first trial of a childhood obesity prevention intervention that: has been developed using the MRC framework for complex interventions, tests both the clinical and cost-effectiveness of a school-based intervention and will have sufficient length of follow-up to examine longer term effects. The trial setting includes a diverse socioeconomic and multi-ethnic population to allow exploration of sub-group effects. There is also consideration of a wide range of outcomes, including psychosocial effects to monitor potential harm.

The trial will address some of the limitations identified in previous research [9], particularly including a sample size large enough to detect clinically significant differences in adiposity, use of an objective measure of physical activity, inclusion of cost effectiveness evaluation, a comprehensive process evaluation and assessment of longer term outcomes (all schools at 18 months and half the schools at 27 months post intervention completion).

Given the pragmatic and complex nature of the trial, it will not be possible to assess intervention efficacy directly or to disentangle the relative contribution of different intervention components to any observed outcomes. On the other hand, assessment of effectiveness in real settings facilitates future intervention roll-out and dissemination, should the intervention prove to be clinically cost-effective. Thus, the study has the potential to influence health and education policy in the UK and further afield.

The comprehensive process evaluation and detailed assessment of implementation alongside the trial will allow us to contextualise and explain the findings of the trial and inform future implementation. It will also allow us to perform analyses to explore the relationship between intervention implementation and outcomes, which has not been undertaken in previous childhood obesity prevention trials.

In addition to the findings of the trial, the study will also provide a large dataset on the weight status and other health indicators of a sub sample of multi-ethnic children in the West Midlands, which can be used to address other relevant research questions.

## Abbreviations

ANGELO: Analysis Grid for Environments Linked to Obesity
BEACHeS: Birmingham healthy Eating and Active lifestyle for CHildren Study
BMI: Body Mass Index
CADET: Child and Diet Evaluation Tool
FSM: Free school meals
ICC: Intraclass correlation coefficient
MRC: Medical Research Council
MVPA: Moderate to vigorous physical activity
NIHR: National Institute for Health Research
PedsQL: Pediatric Quality of Life Inventory
WAVES: West Midlands ActiVe lifestyles and healthy Eating in School children study
VV: Villa Vitality
